**S2 Appendix. English translation of the German study protocol-**

**Background and Rationale**

**1.1 Background**

Renal cell carcinoma (RCC) is the third most common type of urological cancer in in Europe and the USA, with an increasing incidence due to incidental detection (with imaging techniques) of small mass tumors staged T1 [1-4]. A partial nephrectomy (PN) with preservation of nephrons is recommended in early-stage RCCs, under certain circumstances also in with stage T2 [5]. Notwithstanding the nephron-sparing effect of PN compared to radical nephrectomy, postoperative complications are common. This is due to the surgery-related ischemia during hilar clamping and indirect ischemia and reperfusion injury (IRI) involving tumor manipulation and resection itself [6]. Particularly impairment of renal function is common with a clinically significant glomerular filtration rate (GFR) decrease of 16-30% [6-8]. Beside limitations of clamping- and manipulation time, the use of cold ischemia for durations of more than 30 minutes ischemia, administration of mannitol, adequate hydration, avoidance of hypotension and blood loss, a postoperative GFR decline cannot fully be prevented [6-8]. After PN the GFR shows an initial nadir [8], followed by recovery to new reduced baseline levels. Evidence from clinical studies is limited [9], particularly in regard to the early postoperative maximum decrease of the GFR.

A therapeutic approach enhancing kidney-resilience to IRI would be of outstanding clinical relevance.

**1.2 Rationale**

The noble gas xenon (Xe) is approved since 2005 in Germany and 2007 in Europe for clinical routine use as an inhalational anesthetic. It is used for balanced anesthesia together with opioids for adult American Society of Anesthesiologists (ASA) ≤III patients. Different experimental *in vitro* and *in vivo* models were able to demonstrate the neuroprotective and cardioprotective effects induced by Xe treatment [12-15]. Both pre- and post conditioning protocols were effective [16-17]. Nephroprotection by Xe was recently shown in an *in vivo* IRI model and *in vitro* model of glucose deprived injury in human tubular kidney cells [18-19]. Both studies found an increased expression of hypoxia inducible factor-1α (HIF-1α) in the Xe treated cells or kidneys of the animals [18-19]. The nephroprotective effect was abolished by inhibition of HIF-1α activity [18]. Further nephroprotective effects showed Pype et al. Xe-saturated cold storage solutions reduced the ischemia-reperfusion injury after 6 hours of cold ischemia in a rat model of renal transplantation [20]. Animals with Xe-treated kidneys showed better creatinine-clearance after 7 and 14 days and decreased excretion of albumin in urine, which shows the tubular injury [20]. Clinical data from our study group revealed a better renal function in patients undergoing cardiac surgery after Xe anesthesia [21]. Furthermore, we could show that IRI on cardiac surgery patients leads to an enhanced release of macrophage migration- inhibiting factor (MIF) in serum. MIF was associated with an enhanced antioxidative capacity and less postoperative renal failure [22]. Therefore the influence of Xe compared to isoflurane on MIF should be examined in the present study. Beside the experimental organ protective effects, Xe is an effective anesthetic with favorable hemodynamic properties with blood pressure stability and low heart rates [10-11]. Other anesthetics like isoflurane, desflurane, sevoflurane and propofol usually show low blood pressures; with the need of catecholamines during anesthesia. Both low mean arterial pressures as well as the vasoconstrictive drugs like norepinephrine have additional negative influence on the renal function. This could lead to a beneficial risk-benefit ratio for Xe.

Xe is a extremely rare and natural gas, which is linked to higher costs. But a postoperative renal insufficiency is often associated with a longer hospital stay, more costs and higher mortality [23]. Reduction of the postoperative renal insufficiency by Xe, via organ protection or additional hemodynamic stability, could counterbalance the higher costs for Xe.

**1.3 Hypotheses**

The aim of this pilot-study is to compare the GFR decrease after Xe compared to standard anesthesia in patients undergoing PN. GFR should be measured daily until postoperative day 7. GFR and creatinine in serum will be assessed after 3-6 months to determine the longer-term renal function. Data from the control group will be compared to the Xe group. We aim to test our hypothesis, that Xe is more favorable for patients undergoing surgeries with temporarily reduced renal perfusion or clamping. Hereby Xe will induce an attenuated GFR decrease, either by hemodynamic stability before and after renal manipulation or by an unknown nephroprotective effect. Organ protection by Xe is often induced by pre-conditioning, which also protects renal tissue during ischemia. Novelty of our hypothesis is that the impact of anesthesia for nephroprotection during renal surgery was never investigated before. As described before, Xe anesthesia has a great potential to induce clinical significant nephroprotection. Randomized controlled trials are lacking with regard to this issue. We have chosen Iso as the comparative, as it was shown to have the strongest nephroprotective effect against IRI [24-25], compared to sevoflurane or desflurane [26]. Furthermore, Iso does not exhibit potentially nephrotoxic effects like sevoflurane [27] and it was not inferior in clinical studies examining postoperative renal function after major surgery and renal transplantation compared to sevoflurane, desflurane or propofol anesthesia [28-30].

**2 Objectives**

**2.1 Primary objective**

The aim of this project is to analyze a potential nephroprotection by Xe after PN in a randomized controlled pilot-study, by evaluation of the early postoperative GFR decline, compared to isoflurane anesthesia. If we could show a nephroprotective effect, we aim to perform a multicenter randomized controlled trial with a large sample size. The long-term goal is to develop a preventive strategy for attenuation of renal insufficiencies after renal-damaging surgeries (PN, renal transplantation). This could reduce short-term and long-term consequences (short-term dialysis, chronic renal insufficiencies, cardiovascular risk) for the patient and healthcare.

**2.2 Primary endpoint**

The primary endpoint of this study was to determine the maximum GFR decrease between the preoperative value and the lowest value within the first seven postoperative days after PN. GFR was calculated by a combined formula incorporating serum creatinine and serum cystatin C [31-33]. The maximum GFR decrease is calculated as the difference between the baseline GFR minus the lowest GFR within the first seven postoperative days.

**2.3 Secondary objectives/ secondary endpoints**

The following data will be assessed as secondary endpoints: Duration of direct manipulation-/ ischemia time during renal tumor resection; duration of anesthetic exposition before and after tumor resection; intraoperative blood loss, tumor size and histology; optional assessment of HIF 1 activation in healthy surrounding tissue; GFR time-course, determined by cystatin C assessment in serum; creatinine time-course within the first 7 days after PN; optional assessment of KIM-1 or NGAL in urine before and after tumor resection; urine output during surgery and on postoperative day 1-3; acute kidney injury with increasing AKIN-classification is already within 48h associated with increased mortality. This association was verified in several studies. A recent meta-analysis showed a doubled risk for mortality (RR= 2.4) for patients with AKIN I compared to patients without. Furthermore, it is increasing continuously from AKIN II to AKIN III (RR = 4.2 and RR = 6.4, respectively) and further on [35].

Macrophage migration-inhibiting factor (MIF) in serum will be assessed preoperatively, 5 minutes after termination of the tumor ground-treatment, directly postoperative in the PACU and after 24h. Additionally we will assess demographic data like age, height, BMI and anesthesia-related data (anesthetic-concentrations and amount of opioids and inspiratory oxygen-concentration) in this pilot-study. These data will be used to check the comparability of the two groups. According to GCP, safety data like vital patient data (oxygen saturation, blood pressure, heart rate) during anesthesia, laboratory data (blood cell count, coagulation data, urea, transaminases, creatine kinase) after surgery and all adverse events (AEs) und serious adverse events (SAEs) will be assessed in addition. After 3-6 months creatinine in serum and GFR should be determined for longer-term renal function course. This will be achieved by contacting of the familiar physician or urologist during the routine post-surgical care.

**3 Methods**

**3.1 Study design**

The present pilot-study will be a mono-center, prospective randomized controlled phase III study, with a patient and outcome assessor blinded design. It will be conducted in the University Hospital RWTH Aachen

• Group 1: Xenon-group: 60% Xenon/ 40% oxygen inspiratory.

• Group 2: Control-group: 1,2 Vol.% end-expiratory Isoflurane/ 40% oxygen/ air-mix.

All other drugs, which will be used for the standardized anesthesia, will be specified in a standard operating procedure form before patient recruitment.

**3.2 Randomization**

The randomization sequence will be generated computer-based by an independent biometrician. Patients will be randomly allocated according to a computer-based algorithm into the two groups Xe or control. Allocation concealment will be achieved by sequentially numbered, sealed opaque numbered envelopes, which will be kept safe until randomization of the single patients. Patients will be enrolled and pseudonymized with sequential increasing numbers by an investigator after obtaining written informed consent. All data will be collected under this pseudonymized number and only the biometrician and the monitor will have access to the randomization sequence, which includes the allocated treatment (Xe or control). The patients, the outcome-assessing investigator and the surgeon will be blinded (the ventilator will be the same for all patients to prevent accidental un-blinding). Only the second investigator, who performs the anesthesia and the intraoperative data assessing study-nurse, cannot be blinded.

**3.3 Storage of the randomization-codes and un-blinding**

**3.3.1 Premature un-blinding**

During study conduction we will assure complete blinding. The principle investigator or sub-investigator can reverse blinding for patient protection in emergency cases. This un-blinding of the randomization number is restricted to cases of AE or serious adverse events (SAE) with clinical need. Premature un-blinding has to be documented in the patient file and the sponsor will be informed immediately. Emergency drugs and therapy will be administrated according to the medical evidence and usual clinical practice.

**3.3.2 Regular un-blinding**

Regular un-blinding will occur after termination of the study and database lock.

**3.4 Personnel and technical requirements**

**3.4.1 Agreements with researchers with regard to this study**

An agreement was established with the Department of Urology, director of the Department named Univ.-[name]. [name], and the assistant professor Dr. med. [name]. The Department of Urology will perform PN and look after the patients. Furthermore, there is an research agreement with the Institute of Pathology (director: Univ.- [name]. med. [name]). The Institute of Pathology will routinely determinate the size and histology of the resected tissue. Optionally for this study they will determine HIF 1α in the healthy surrounding tissue by immunohistochemistry and KIM-1 or NGAL in urine by ELISA, in addition.

A further cooperation is established with the Institute of Medical Statistics, Informatics and Epidemiology (IMSIE), university of cologne (director Univ.-[name]. rer. nat. [name]). This Institute will provide the responsible biostatistician for the randomization, the GCP-conform data verification, -storage, and analysis.

**3.4.2 Technical equipment**

All technical devices, which are required for this project, are present in the involved institutes and departments. In particular the specific ventilator for Xe anesthesia and control anesthesia conduction (Felix Dual, Taema, ALMS, France) is available in the anesthesia department. Further standardized anesthesia equipment as well as the equipment for surgery and histopathology analysis is available in the participating departments. A certified local laboratory for determination of the laboratory variables is present in the University Hospital. There are plenty of computers for data entering, analysis and manuscript writing available in the Department of Anesthesia and the Medical Statistics, Informatics and Epidemiology Institute. The required software (SPSS and randomization software) is also available.

**4 Study population**

**4.1 Study- and intervention duration**

The study duration will last for each patient from the moment of the written informed consent until the discharge date or maximum the seventh postoperative day. Depending on the surgery time-point this will be 8-10 days. After 3-6 months we will assess the creatinine in serum and GFR, if measured by the family physician or urologist. The intervention duration will correspond to the anesthesia duration for the respective surgery, which will commonly be around 3 hours. The total recruitment period (first patient in to last patient out) is planned for sixteen months.

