Investigator II will document all assessed data in the paper-based CRF of the respective patient. Follow-up during the hospital stay will last a maximum of seven postoperative days. Urine output will be assessed every 6 hours after surgery via urine catheter. The total urine output will be assessed in the second postoperative day. Urine samples will be collected on the first and second, as well as the seventh postoperative day for optional additional analyses (KIM-1 or NGAL by ELISA). Blood samples will be drawn each morning from the first until the discharge day or maximum 7^th^ postoperative day. Furthermore, the investigator will measure vital function (blood pressure, heart rate, oxygen saturation) daily. Cystatin C will be determined from the blood samples and the GFR will be calculated using cystatin C. Furthermore, the secondary blood outcome variables (creatinine, blood cell count, coagulation, urea in serum, transaminases and creatine kinase) will be determined in the blood samples. A further blood sample will be drawn on the first postoperative day for MIF determination in serum. The investigator will value and document laboratory variables and the amount of urine output in the respective CRF. In addition, the investigator will determine an acute renal failure according to the AKIN criteria [34] on the first and second postoperative day. In-hospital study participation is terminated after physical examination on the discharge day or maximum the 7^th^ postoperative day. We will try to obtain the GFR and creatinine value after 3-6 months postoperative by contacting of the family physician or attending urologist.

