**5.3.7 Visit 10 (3-6 months postoperative)**

- Contacting of the family physician or attending urologist, to obtain the GFR and creatinine value, which was probably measured during the clinical postoperative routine.

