**7.1.3 Secondary outcomes**

The following secondary outcomes will be assessed in addition for the comparison of Xe anesthesia to isoflurane anesthesia:

- Measurement of the anesthesia and safety variables every 5 minutes and the determination of urine output at the end of surgery.
- Acute kidney failure determination according to the AKIN criteria, by measurement of the urine output every 6 hours until the second postoperative day, total urine output on the second postoperative day and determination of creatinine within the first 7 postoperative days or if earlier the day of discharge, respectively.
- Daily assessment of the safety data (creatinine, blood cell count, coagulation, urea in serum, transaminases and creatine kinase) until the 7^th^ postoperative day or if earlier the discharge day, respectively.
- Patients` vital data (blood pressure, heart rate, oxygen saturation) until the 7^th^ postoperative day or the discharge day (if earlier), respectively.
- Histological analysis with immunohistochemistry in paraffin sections and optional determination of HIF-1α in the tumor-free surrounding tissue via immunofluorescence staining.
- Determination of migration-inhibiting factor  (MIF) in serum.
- Determination of KIM-1 or NGAL in urine.
- Assessment of intraoperative blood loss.
- Assessment the anesthesia time until the beginning of the surgical ischemia (tumor resection time) and after the end of this surgical ischemia (defined by the termination of the tumor ground-treatment), until cessation of anesthesia. This will be assessed in collaboration of the investigator and the surgeons.
- Assessment of GFR and creatinine in serum after 3-6 months postoperative.

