**9.3 Statistical analysis**

All data will be collected descriptively according to the study protocol. After verification of the data in the SPSS-data base, they will be provided to the biometric institute (IMSIE, Cologne). A covariance-analysis will be used for analysis of the primary outcome GFR, by comparison of the data in the isoflurane- and Xe group for each time-point. The primary outcome, max. variation of the GFR, will be calculated according to 2.3.4. This primary outcome will be primary analyzed by covariance-analysis with the factor group and the covariate baseline value, with a 2-sided Mann- Whitney-Test with the level of 5%. Primary analysis will be performed according to the Intention-to-treat principle (missing values will be replaced by imputations, which will be pre-defined in a statistical analysis plan. This enables a conservative estimate of the effect). Secondary outcomes will be analyzed according to the per protocol analysis. Other variables will be analyzed descriptive and explorative with the common 2-sample T-test. Descriptive analysis for baseline and outcome variables will be performed with the usual measured values and parameters, graphics and tests (p-values) depending on the scale levels of the variables.

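### The 3-6 month renal outcome has no study-arranged measurement, so an unknown and possibly selective share of patients will lack a value

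*Protocol*

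**What the plan says.** Section 1.3 states the aim without condition: "GFR and creatinine in serum will be assessed after 3-6 months to determine the longer-term renal function". Section 7.1.3 lists the same item among the secondary outcomes for the comparison of the two anesthetics: "Assessment of GFR and creatinine in serum after 3-6 months postoperative".

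The collection rules are weaker. Section 4.1 reads "After 3-6 months we will assess the creatinine in serum and GFR, if measured by the family physician or urologist". The follow-up text in 5.3.2 reads "We will try to obtain the GFR and creatinine value after 3-6 months postoperative by contacting of the family physician or attending urologist". Visit 10 (5.3.7) consists of contacting the outside physician for a value "which was probably measured during the clinical postoperative routine". Section 2.3 is more confident and expects the value from routine care: "This will be achieved by contacting of the familiar physician or urologist during the routine post-surgical care".

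On analysis, 9.3 ties imputation to the primary intention-to-treat analysis and leaves its details to a statistical analysis plan. It then assigns secondary outcomes to a per-protocol analysis and adds: "Other variables will be analyzed descriptive and explorative with the common 2-sample T-test". Section 9.2 includes all randomized patients in the analysis. Section 9.4 says that remaining missing data follow the intention-to-treat principle, without naming a method.

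**The concern.** This is the only outcome after day 7. It is the only one that bears on the long-term goal in 2.1, which includes fewer chronic renal insufficiencies. Section 1.1 describes an early nadir followed by recovery to a lower level, so the late value is what shows whether an early benefit lasts.

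The study neither draws a sample nor asks for one; it takes what exists. Two things follow. First, an unknown number of values will be absent, and no analysis rule can recover a test that was never done. Second, the outside physician who decides whether to measure may know how the kidney did in hospital. If that knowledge matters, having a value depends on the early GFR loss, a post-randomization variable that treatment is meant to change. The patients with values would then no longer be a randomized comparison, and a pilot meant to inform a larger trial would carry an incomplete and possibly attenuated late result.

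**Working it through.** **Plan's own figure.** The documents give no figure for the 3-6 month outcome, so the reference is the signal rule in 9.1: 25 per group, standardized difference 0.6, two-sided 20%, power 80%. With power = Φ(0.6·√(n/2) − z) and z = 1.2816, n = 25 gives Φ(2.121 − 1.282) = 0.799. The figure is reproduced.

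**Loss of precision.** The same formula, with a share of the 25 per arm measured at random:

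| Share measured | n per arm | Power, two-sided 20% | Power, two-sided 5% |
|---|---|---|---|
| 100% | 25 | 80% | 56% |
| 80% | 20 | 73% | 48% |
| 60% | 15 | 64% | 38% |
| 50% | 12.5 | 59% | 32% |

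The standardized difference of 0.6 is borrowed from the primary endpoint; the documents give none for the late outcome.

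**Possible bias, graded selection.** From 9.1: early GFR decrease 54 (control) and 36 (xenon) ml/min/1.73 m². Assumed: SD of early decrease 30; true late difference 9 with SD 15; correlation of early and late loss 0.3 or 0.6; 50% or 80% measured overall; log-odds of being measured linear in early decrease. Late difference among measured patients, compared with the true difference:

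| Log-odds per 30 ml/min | Change in arm difference |
|---|---|
| 0 | none |
| 0.5 | −1% to −3% |
| 1 | −3% to −10% |
| 2 | −7% to −22% |
| −1 (good course measured more often) | −3% to −10% |

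At slope 1 with 50% measured overall, 56% of controls and 44% of xenon patients have a value. Weighting by the true probability of being measured restores about 9.0 (8.9 to 9.05).

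**Possible bias, threshold selection.** The 54 in 9.1, read as a 30% decrease, implies a baseline of 54/0.30 = 180. The second model therefore uses the percentages with a more usual baseline. Taken from 9.1: early loss 30% versus 20%, reading the 10% smaller decrease as percentage points. Assumed: baseline GFR 90 (SD 15, floor 60); SD of loss 8 to 15 percentage points; 40% or 60% of the loss persisting; residual SD 6; measurement depending on whether early loss exceeds 25%.

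| Measured if loss ≤25% / >25% | Change in arm difference |
|---|---|
| 30% / 90% | −13% to −15% |
| 40% / 90% | −7% to −9% |
| 50% / 70% | −1% to −2% |
| 95% / 95% | none |
| 90% / 30% (reverse) | −13% to −15% |

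Example: 30%/90%, SD 15 points, 60% persisting. Measured share is 68% of controls and 52% of xenon patients; the difference falls from 5.4 to 4.6 ml/min/1.73 m².

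In both models selection on early loss in either direction pulls the difference toward zero. The strength of selection, which the documents do not give, sets the size.

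**The case against.** The strongest reply is that this is an openly stated choice. A pilot uses routine follow-up data and says so. Sections 2.3 and 5.3.7 describe the same postoperative routine for all patients, who were all operated on for suspected renal carcinoma. If that routine includes creatinine for nearly everyone, there is little missing and no bias. This stands, and it is why the bias is put as a possibility.

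Two stronger readings are tempting. A reader might infer that patients with a poor early course will be over-represented. No section gives a measurement pattern or links measurement to early GFR. A reader might also infer from 9.3 that only measured patients will be compared. Per protocol defines an analysis set by adherence; it is not a rule for missing values. Sections 9.2 and 9.4 point to all randomized patients, and the imputation rules may be in a statistical analysis plan that is not at hand. A measured-only comparison is a plausible reading but is not stated.

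The bias is also small against sampling error. In the example above it is 5.4 − 4.6 = 0.8. With about 17 and 13 patients measured and an assumed SD of 10 to 15, the standard error is SD·√(1/17 + 1/13) = 3.7 to 5.5, so the bias is about 0.15 to 0.22 standard errors. A null late result would be likely even with complete data and should not be blamed on who was measured.

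What the reply does not answer is the collection rule itself. It belongs in the protocol, and 9.4 cannot repair it: entering missing items from source data does not help when the test was never done.

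**Conclusion.** The point holds in a limited form. A stated aim and listed secondary outcome is left to outside care, with no study-arranged measurement, so the share of patients with a value is unknown and may be related to the early course. The certain cost is precision, in proportion to the values lost. The possible cost is attenuation of the arm difference if only measured patients are compared: roughly 0-15% in most assumed scenarios, about 20% with steep selection and strong early-late correlation, and none if nearly everyone is measured. These ranges rest on assumed selection, SDs and persistence, none of which the documents give. The early decreases alone come from 9.1. The primary endpoint, measured in hospital, is untouched. The change is worth making because it is cheap and this is the trial's only late outcome.

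**What to change.** **Collection (main change).** In 4.1, 5.3.2 and 5.3.7, replace the conditional wording with a standard request in every patient's discharge letter, identical in both arms, that serum creatinine be included in the routine 3-6 month follow-up. Report the number measured per arm.

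**Analysis (secondary, since details may sit in the statistical analysis plan).** In 9.3, state that this outcome is analysed in all randomized patients using the baseline and in-hospital values, by a mixed model for repeated measures or multiple imputation, with the measured-only comparison as a sensitivity analysis. Creatinine is already drawn daily in hospital (8.2.2), so the predictors exist. Reconcile this with the per-protocol sentence in 9.3 and with 9.2 and 9.4, which now point in different directions.

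**Cost.** One line in the letter and slightly more analysis work; no extra study visit. The model relies on values being missing at random given the in-hospital course, which cannot be verified. That is a further reason to put the collection change first.
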